## Abstract

**Background:**

As a result of the ageing population, there is an urgent need for innovation in community health-care in order to achieve sustainability. Reablement is implemented in primary care in some Western countries to help meet these challenges. However, evidence to support the use of such home-based rehabilitation is limited. Reablement focuses on early, time-intensive, multidisciplinary, multi-component and individualised home-based rehabilitation for older adults with functional decline. The aim of this study is to investigate the effectiveness of reablement in home-dwelling adults compared with standard treatment in relation to daily activities, physical functioning, health-related quality of life, use of health-care services, and costs.

**Methods/Design:**

The study will be a 1:1 parallel-group randomised controlled superiority trial conducted in a rural municipality in Norway. The experimental group will be offered reablement and the control group offered standard treatment. A computer-generated permuted block randomisation sequence, with randomly selected block sizes, will be used for allocation. Neither participants nor health-care providers will be blinded, however all research assistants and researchers will be blinded. The sample size will consist of 60 participants. People will be eligible if they are home-dwelling, over 18 years of age, understand Norwegian and have functional decline. The exclusion criteria will be people in need of institution-based rehabilitation or nursing home placement, and people who are terminally ill or cognitively reduced. The primary outcome will be self-perceived performance, and satisfaction with performance of daily activities, assessed with the Canadian Occupational Performance Measure. In addition, physical capacity, health-related quality of life, use of health-care services, and cost data will be collected at baseline, and after 3 and 9 months in both groups, and again after 15 months in the intervention group. Data will be analysed on an intention-to-treat basis using a linear mixed model for repeated measures.

**Discussion:**

The findings will make an important contribution to evaluating cost-effective and evidence-based rehabilitation approaches for community-dwelling adults.

**Trial registration:**

The trial was registered in ClinicalTrials.gov November 20, 2012, identifier:
NCT02043262.

## Background

The increasing aged population, in conjunction with an expected shortage of health-care personnel in developed countries, present a huge challenge to the containment of future health-care costs
[1]. Further, in times of budget cuts to front-line public services, policy makers are seeking new approaches to get more for less by investing the resources available in ways which have an optimal impact on outcomes
[2]. As a result, in recent years, there has been an increasing interest in home-care reablement services (hereafter ‘reablement’)
[3]. Reablement, termed ‘restorative care’ in US, Australia and New Zealand, is an approach to improve home-care services for older people needing care or experiencing functional decline. It is a goal-directed and intensive intervention, which takes place in the person’s home and local surroundings with a focus on enhancing performance of everyday activities defined as important by the person. The intention is to increase independence in daily activities, and enable people to age in place, be active and participate socially and societally. The health-care providers are organised in an integrated, coordinated multidisciplinary team that works together with the person towards shared goals
[4]. In Norway, a substantial proportion of municipalities are currently implementing reablement.

The effects of reablement have so far been evaluated in three randomised controlled trials (RCTs). Two of these were conducted in New Zealand, and the results showed improved social support and physical functioning
[5] and improved quality of life
[6]. In a third Australian RCT with 750 participants and a 2-year follow-up, reablement was compared with usual care
[7]. Even if the results showed few differences between groups in individual outcomes over time, a significantly smaller proportion of the reablement group required assistance with personal care. In a later publication from the same trial, the results showed that participants in the reablement group required fewer home-care hours, were less likely to be approved for a higher level of aged care such as nursing homes, and were less likely to be in need of emergency department treatment than the conventional care group
[8]. The results thereby indicate that reablement may reduce the need for ongoing home-care, as well as for other health care services.

Two studies have investigated cost-effectiveness of reablement. The results in a large British non-randomised study with 1015 participants showed no significant differences between the intervention and control groups with respect to cost savings
[9]. However, the results in the aforementioned Australian RCT showed that aggregated health and home-care costs of reablement were lower than the costs of the conventional home-care
[8].

In summary, the research on the effectiveness of reablement is scarce, the results are conflicting and more studies are needed.

### Aims and research questions for the study

The main objective will be to evaluate health effects and cost-effectiveness of a reablement intervention compared with current standard treatment for home-dwelling adults experiencing functional decline.

More specifically, our study will answer the following research questions:Is reablement more effective with regard to performance and satisfaction with performance of daily activities, physical functioning, and health-related quality of life compared with standard treatment?Does the experimental intervention or the control intervention provide more cost-effective use of health-care resources?

## Methods/Design

### Study design and setting

This will be a parallel-group randomised controlled superiority trial in which all participants will be assessed at baseline, and after 3 and 9 months. Participants in the intervention group will also be re-assessed after 15 months. The study will be conducted in a primary care setting in a rural municipality in Norway with approximately 14,000 inhabitants. The intervention group will receive reablement and the control group will receive standard treatment and care. For ethical reasons, the control group will be offered reablement 9 months after baseline assessment. Thus, potential long-term effects data at 15 months after baseline will only be collected from the experimental group. The flow diagram of the study protocol is outlined in Figure 
1. The protocol employs relevant standard protocol items for clinical trials according to the SPIRIT 2013 statement
[10], and follows the CONSORT statement
[11] for transparent reporting. The trial is registered in ClinicalTrials.gov, identifier NCT02043262.

**Figure 1 Fig1:**
[figure not shown]
**Flow diagram of study protocol.**

### Participants and eligibility criteria

People applying for, or referred to, home-based services are potential participants in the study. Health-care providers in a central office responsible for the allocation of public health-services in the municipality will identify potential participants amongst the applicants, inform them about the new reablement service, and invite them to participate. Those who are interested will be screened for eligibility, and in order to enrol, participants will have to give their written informed consent. An additional strategy to achieve adequate participant enrolment to reach target sample size will be self-selection through advertisements.

We will include home-dwelling persons over the age of 18 years, who currently live in the municipality, are able to understand Norwegian, and have a functional decline in one or more daily activities. To enhance recruitment, the study will not be restricted to older adults even though we expect the majority of participants to be in that age group. We will exclude participants if they are in need of institution-based rehabilitation or a nursing home placement, are terminally ill, or are moderately or severely cognitively reduced (subjectively assessed by health-care providers based on observation and communication).

### Randomization and allocation concealment

A bio-statistician (BE), not involved in the assignment of participants to groups, will perform the randomisation with an allocation ratio of 1:1 using a computer-generated permuted block randomisation sequence, with randomly selected block sizes. We will conceal the allocation sequence in sequentially numbered, opaque, sealed envelopes. The allocation list will be stored in a safe deposit box in a central office in the municipality. After baseline assessments, but still in the home of the participant, the research assistant will randomly assign the participant to one of the two trial groups, by means of calling the central office. The health-care provider in this office will unlock the safe deposit box containing the allocation list and reveal information on the particular participant’s group assignment. To prevent subversion of the allocation sequence, the name of the participant will be written on the envelope after disclosing group assignment in each case. Hence, neither health-care providers enrolling participants nor research assistants will have influence on group assignment.

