### Blinding

Occupational therapists and physiotherapists in the municipality will conduct the baseline assessments in the participant’s home prior to randomisation. The research assistants, who are also occupational therapists and physiotherapists, will be blinded to group allocation and perform all follow-up assessments. The research assistants will urge the participants not to reveal their group allocation during follow-up assessments, which will also take place in the participant`s home. The success of research assistant blinding will be evaluated for both follow-ups. Due to the nature of the interventions, it will not be possible to blind participants and health-care providers. Researchers performing data entry and data analysis will, however, be blinded to group allocation.

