### Outcomes

Data collection will involve the use of four different outcomes measures. In addition, cost outcomes in terms of consumption of different home-based services will be registered on a daily basis during the first 9 months after inclusion. This comprises registering minutes spent by different health professionals in the participant’s home. The first author will train all research assistants in how to conduct the data collection in order to obtain protocol adherence. Table 
2 provides an overview of the various outcomes that will be measured.

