**Health-care services and cost measures**		
Warranted community-based assistance in time of inclusion	*Type of assistance wanted*	t1
	Home-helper/Nurse/Auxiliary nurse/Occupational therapist/Physiotherapist/Nursing home placement long term/Nursing home placement short term/Assisted living/Meals on Wheels/Safety alarm/Rehabilitation	
Inpatient and outpatient treatment since last assessment	*Frequency and type of co-interventions*	t2, t3
	Hospital admissions/Admissions to other institutions/Day centre placement/Outpatient treatment	
Current home-based assistance offered	*Presence and frequency of home-based assistance*	t2, t3, t4
	Home-helper/Nurse/Auxiliary nurse/Occupational therapist/Physiotherapist/Meals on Wheels/Reablement/No assistance	
Current community institution-based service offered	*Type of institution-based service offered*	t4
	Nursing home placement long-term/Nursing home placement short-term/Day placement/Other institution placement/No institution placement	
Usage of home-based services	*Daily time registration in minutes of working time used during home-visits*	t5
	Home-helper/Nurse/Auxiliary nurse/Occupational therapist/Physiotherapist/Social educator/Assistant/Speech therapist/Student	

t1 = baseline assessment, t2 = 3 months after baseline assessment, t3 = 9 months after baseline assessment, t4 = 15 months after baseline assessment, t5 = daily assessment during 9 months after baseline assessment.

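### The protocol has the research assistant obtain the allocation by phone, yet declares the research assistants blinded assessors for all follow-ups; the passages must be reconciled

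*Protocol article*

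**What the plan says.** Four places in the protocol article bear on this.

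- **Randomization and allocation concealment.** After the baseline assessments, while still in the participant's home, "the research assistant will randomly assign the participant to one of the two trial groups, by means of calling the central office". A provider there opens the deposit box and will "reveal information on the particular participant’s group assignment".
- **Blinding.** "Occupational therapists and physiotherapists in the municipality will conduct the baseline assessments in the participant’s home prior to randomisation". The research assistants are described separately, as also being occupational therapists and physiotherapists, and they "will be blinded to group allocation and perform all follow-up assessments". They are to urge participants not to disclose their group, and the success of their blinding is to be evaluated at both follow-ups.
- **Abstract, Methods/Design.** The claim is made without exception: "all research assistants and researchers will be blinded".
- **Table 2, health-care services and cost measures.** Current home-based assistance is recorded at 3, 9 and 15 months with the categories "Home-helper/Nurse/Auxiliary nurse/Occupational therapist/Physiotherapist/Meals on Wheels/Reablement/No assistance". The table does not say who records the item or from what source. The Outcomes section says: "The first author will train all research assistants in how to conduct the data collection".

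**The concern.** One named role appears on both sides of the blind. The research assistant makes the call on which the group is disclosed, and the research assistants are the blinded assessors at 3 and 9 months. Staff who follow the randomisation section to the letter would tell an assessor the allocation on the day of randomisation.

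Participants and care providers are not blinded, so assessor blinding is the main protection left at the point of outcome measurement. The COPM is scored in a semi-structured interview. In the Timed Up and Go the participant is encouraged to walk fast, and in the grip test to squeeze as hard as possible. An assessor who knows the group can influence prompting and encouragement. The planned check of blinding success would detect such a failure but not prevent it, and an assessor who has been told the group cannot be blinded again.

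The 3-month service item raises a smaller, related concern. If the assessor asks it, the visit that scores the outcomes also asks whether the participant is receiving reablement.

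**Working it through.** **The allocation call**

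1. *Who is in the home at randomisation?* The randomisation section says the research assistant. The Blinding section says the baseline visit is made by municipal therapists, whom it describes separately from the research assistants. The two disagree.
2. *Who learns the group?* The office discloses it in response to the call. The recipient is not named, but the caller is the research assistant. That the caller hears the result is a near-certain inference, not a quotation.
3. *Is the caller kept from the result, or from that participant's follow-up?* No section says either.
4. *What is claimed?* All research assistants are blinded, and they do all follow-up assessments.

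Steps 2 and 4 cannot both hold under one meaning of the term, unless the caller is kept from hearing the result, which step 3 does not provide for.

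**The service item, by time point**

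| Visit | What an entry of reablement would show |
|---|---|
| 3 months | Controls are offered reablement only 9 months after baseline (Study design and setting), so an entry points to the intervention arm. The programme lasts at most 3 months and may already have ended, so the entry need not appear for every intervention participant. |
| 9 months | The programme should be over in the intervention arm and controls are becoming eligible. The entry does not identify the intervention arm. |
| 15 months | Only the intervention group is followed, so the question does not arise. |

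**Size, as an illustration only**

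Inputs from the Sample size calculation section: SD 2.5, difference 2 points, two-sided 5%, power 80%, within-subject correlation 0.7, 21 per group.

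- Reproducing the 21: for a single measurement, n = 2 × [2.5 × (1.960 + 0.842) / 2]² = 24.53 per group. Averaging m measurements multiplies this by (1 + (m − 1) × 0.7) / m. For m = 2 the factor is 0.85, and 24.53 × 0.85 = 20.85, or 21. For m = 3 the factor is 0.80, which gives 19.6, or 20. The stated 21 therefore reproduces with two measurements.
- SD of the two-measurement mean: 2.5 × √0.85 = 2.305.
- Standard error of the group difference: 2.305 × √(2/21) = 0.711.
- Assumed assessor shift of 0.5 points, a quarter of the 2-point target: 0.5 / 0.711 = 0.70. P(|Z + 0.70| > 1.96) = 0.104 + 0.004 = 0.108.
- Assumed shift of 0.25 points: 0.25 / 0.711 = 0.35, and the same probability is about 0.064.

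The shifts are assumptions with no source in the documents. The contradiction does not depend on them.

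**The case against.** The strongest defence is that the research assistant in the randomisation section is a loose label for the municipal therapist who has just done the baseline visit. The call is made straight after baseline, in the home, and the Blinding section puts the municipal therapist there. On that reading no follow-up assessor is told the group, and the fault is one of naming. Even on the literal reading, no section says that the caller later assesses the same participant. A reader might infer that assessors will in fact be unblinded; the documents do not establish that.

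This narrows the point but does not remove it. The Blinding section uses the term for the blinded assessors, and the randomisation section itself separates research assistants from the providers who enrol participants. On either reading the two sections conflict, and neither contains the safeguard that would make the conflict harmless.

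On the service item, the objection largely stands. Table 2 names no recorder, and municipal records could supply what assistance is offered. Collection by the assessor is plausible from the Outcomes and Blinding sections but is not stated. A reader might also see a leak at 9 months, but the 3-month limit on the programme and the offer to controls from 9 months rule that out.

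Two further inferences go too far. Assessor blinding is not the only blinding claimed: data entry, data analysis and the monitoring bio-statistician are also described as blinded. Nor could an assessor be said to shift every outcome: participants give the COPM ratings themselves, and COOP/Wonka is self-reported. Participants know their group, a limitation the Discussion already discloses, and any assessor effect would come on top of that.

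**Conclusion.** The point holds as a contradiction in the text. The role that obtains the allocation is the role declared blinded for all follow-ups, and nothing in the article keeps the two apart. Followed literally, the randomisation section unblinds an assessor. Read charitably, it misnames who receives the allocation and still has to be corrected.

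The 3-month service item is a secondary risk. It arises only if the assessor asks the item or if researchers doing blinded data entry see it, and only for participants still recorded as receiving reablement.

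The size of any bias cannot be taken from the documents. Under assumed assessor shifts of 0.25 and 0.5 COPM points, the two-sided type I error would be about 6% and 11% instead of 5%. These figures illustrate sensitivity and do not estimate what will happen.

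**What to change.** 1. In the randomisation section, state that the municipal therapist who did the baseline visit, or another person who does no follow-up assessments, makes the call and receives the result. Add that no follow-up assessor is told the allocation.
2. Use one term for the baseline assessors and another for the follow-up assessors throughout, so that the randomisation section, the Blinding section and the abstract agree.
3. Take the 3-month item on current home-based assistance from municipal records. Failing that, ask it after COPM, Timed Up and Go, grip strength, COOP/Wonka and the allocation-guess form are complete, on a separate sheet kept from blinded data entry.

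The cost is reassigning one phone call among existing staff and moving one form item. The first change has to be in place before participants are randomised, because a disclosed allocation cannot be withdrawn.

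### Naming the envelope after the group is disclosed cannot prevent subversion of the allocation, and custody of the allocation list is left unclear

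*Protocol article*

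**What the plan says.** Under Randomization and allocation concealment, the protocol article has a bio-statistician who takes no part in assignment generate a 1:1 permuted-block sequence with random block sizes. Two descriptions of how the sequence is held follow. One is by envelope: "We will conceal the allocation sequence in sequentially numbered, opaque, sealed envelopes". The other is by list: "The allocation list will be stored in a safe deposit box in a central office in the municipality".

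Once the baseline assessment is done, the research assistant telephones that office from the participant's home. Then: "The health-care provider in this office will unlock the safe deposit box containing the allocation list" and discloses the group. The protective step is given as: "To prevent subversion of the allocation sequence, the name of the participant will be written on the envelope after disclosing group assignment". From this the section concludes: "Hence, neither health-care providers enrolling participants nor research assistants will have influence on group assignment".

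Under Participants and eligibility criteria, recruitment is described: "Health-care providers in a central office responsible for the allocation of public health-services in the municipality will identify potential participants". The same providers inform and invite the candidates. The section does not say who carries out the formal eligibility screening. It does say that the cognitive exclusion is a subjective judgement by health-care providers.

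**The concern.** An envelope system resists subversion when each participant is irrevocably tied to the next number before anyone knows what it contains. Here the tie is made once the content is known. If an assignment is unwelcome, the envelope could be set aside or another one used before any name exists, so the step named as the protection leaves that route open.

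The second issue is custody. If a readable list is in the box, and if the people who open the box also decide whom to invite, upcoming assignments could influence who is approached and when. Random block sizes limit guessing from past assignments, but do nothing against someone who can read the sequence.

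This matters more here than in many trials. Participants and providers are unblinded, the primary outcome is self-rated COPM performance and satisfaction, one exclusion criterion rests on judgement, and there are only 30 people per group. A few steered assignments could make the groups differ for reasons other than treatment.

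**Working it through.** The protocol gives no figure on this point to reproduce. The check is mainly one of reading the sections against each other.

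**Step 1: purpose against order.** The stated purpose is "To prevent subversion of the allocation sequence". The stated order is that "the name of the participant will be written on the envelope after disclosing group assignment in each case". For the purpose to be met, the participant's identity must be fixed to the number before opening. In the stated order it is fixed after opening. The step documents the outcome and does not constrain it.

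**Step 2: the conclusion.** The assurance of no influence is introduced as a consequence of the preceding steps. Those that help are independent generation, opaque numbered envelopes, a locked box, and a call made only after baseline. The naming step adds no prior commitment, and it is the one expressly offered against subversion. The assurance is therefore not supported by it.

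**Step 3: list or envelopes.** The section says that the sequence is in sealed envelopes, that a list is in the box, that the box containing the list is unlocked at each call, and that a name goes on an envelope. Two readings fit:

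- The list is loose wording for the set of envelopes, and no future assignment is visible.
- A readable list lies in the box, and future assignments are visible to whoever opens it.

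The text does not decide between them.

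**Step 4: the office.** The recruitment section and the randomisation section each speak of a central office in the municipality, each staffed by health-care providers. Neither says the offices or the individuals are the same, and neither says they differ. Overlap is possible but not established.

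**Step 5: illustration of size.** The protocol supplies 30 per group, a clinically relevant change of 2 points and a conservative SD of 2.5. The number of steered places, k, and their outcome advantage, d, are my assumptions.

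- One group enriched: shift = k × d / 30.
- The same people exchanged between groups: shift = 2 × k × d / 30.

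| k | d (points) | One group enriched | Exchanged |
|---|---|---|---|
| 1 | 1 | 0.03 | 0.07 |
| 1 | 2 | 0.07 | 0.13 |
| 3 | 2 | 0.20 | 0.40 |

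Against the 2-point target, the last row is 0.20/2 = 10% and 0.40/2 = 20%. The unadjusted standard error of the difference with 30 per group is 2.5 × √(2/30) = 0.65, so the same row is 0.20/0.65 = 0.3 and 0.40/0.65 = 0.6 of one standard error. All of this is before baseline adjustment.

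**The case against.** The strongest reply is that the procedure has real protections and that the text can be read harmlessly. The sequence comes from an uninvolved bio-statistician, the envelopes are numbered, opaque and sealed, and the box is locked. The call comes from the participant's home after baseline data exist, so a diverted assignment would probably leave envelope numbers out of step with baseline dates. It would not be invisible.

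A reader might go further and infer that recruiters can see all 60 assignments before enrolment. The documents do not support that. It needs a readable list in the box, and it needs the person opening the box to be one of those who invite. Neither is stated. Nor does the article say that the office screens for eligibility; it says that its providers identify, inform and invite.

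A reader might also hold that any resulting bias would be beyond repair. That is too absolute. Baseline COPM, Timed Up and Go, grip strength and motivation for rehabilitation are all recorded, and the Analysis of effectiveness section adjusts for baseline measurements and adds imbalanced characteristics to the model. Adjustment can reduce bias acting through measured variables; it cannot be relied on for the unmeasured part.

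It can also be said that custody details are often left to a fuller protocol. That has some force for audit and storage arrangements. It does not cover the naming step, because the article itself states the step, its timing, its purpose and the conclusion drawn.

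These replies narrow the point. None of them makes a name written after disclosure act as a prior commitment.

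**Conclusion.** The naming step is wrong as written. It comes too late to do what the protocol says it does, and the assurance that neither enrolling providers nor research assistants can affect assignment is not supported by it. This conclusion rests on the wording alone and holds whether or not the two central offices are the same.

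The custody point is an ambiguity that needs resolving: the text does not exclude that staff who identify and invite participants can reach upcoming assignments, and it does not show that they can. Nothing in the documents indicates that subversion is planned or has taken place.

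The size of any bias cannot be derived from the documents. The 0.2 to 0.4 point shift is an illustration that assumes 3 steered places of 30 and a 2-point advantage, before baseline adjustment; smaller assumptions give much less. The case for the change rests on the logic of concealment and the small cost of the correction, not on that figure.

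**What to change.** Make three changes in the randomisation section:

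1. Reverse the order. On receiving the call, the office records participant ID, date and time on the next sequentially numbered sealed envelope, or in a log against its number, before opening it.
2. State that the municipal box holds only sealed envelopes and that the bio-statistician keeps the readable list.
3. State that the box is opened by existing staff who do not identify or invite participants, and say whether the two references to a central office mean the same office.

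Then reword the closing assurance so that it rests on these steps.

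The cost is a small change in procedure and in where one document is kept. Sample size, assessments and analysis are unaffected. In a municipality of about 14,000 inhabitants, naming a member of staff outside recruitment may take some arranging.
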